### Statistics

The number of evaluable patients (the sample size) is based on Simon’s two stages Mini-max design [26]. This design ensures early study termination if there is insufficient effect. Patients will be evaluated with CT scans every 9 weeks. In randomized trials on second-line therapy, PFS is around 4 months. A tumor control rate less than 10 % after 4 months (at the time of the second evaluation CT scan) is not clinically relevant. Assuming a significance level at 0.05 (α = 0.05) and a power at 80 % (β = 0.20) it can be calculated, that 15 patients should be included in the first part of the study. The enrolment will continue until 15 patients have completed the second CT scan or experienced progressive disease. If none out of the first 15 consecutive patients achieve stable disease at the second CT scan (i.e. after 6 courses of epirubicin), we will reject our hypotheses and close the study after the first stage of accrual. If one or more patients achieve tumor control (partial response or stable disease) at the second scan, an additional 10 patients will be accrued in the second stage. If 5 out of 25 patients achieve tumor control after six courses of therapy, a tumor control rate of 30 % cannot be rejected, and it will be concluded that the treatment is effective enough to continue with future studies.

We will use non-parametric methods for calculation of patient characteristics, side effects and disease control. PFS and OS will be calculated and reported as median survival (Kaplan-Meier method).

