## Background

Colorectal cancer (CRC) is a major health problem since it is among the five most prevalent cancers [1, 2]. Over the last decade, the use of novel treatment modalities and complex treatment strategies in terms of optimized surgery, adjuvant chemotherapy, and novel targeted biological agents have contributed to significant improvement of outcome of the entire population of patients with CRC. However, only three cytotoxic drugs (fluorouracil (5-FU), oxaliplatin and irinotecan) are recommended as standard treatment in patients with metastatic CRC (mCRC). In Europe, the routine clinical management of patients with primary CRC involves adjuvant treatment with 5-FU/Leucovorin (LV) and oxaliplatin (FOLFOX, FLOX or XELOX) given to high-risk patients [3–6]. In the treatment of mCRC, patients who have yet not received oxaliplatin will often be offered FOLFOX, FLOX or XELOX, followed by 5-FU/LV and irinotecan (FOLFIRI, FLIRI or XELIRI) at progression, or vice versa [7–10]. Chemotherapy may be combined with the EGF-receptor targeting antibodies cetuximab or panitumumab in patients with *RAS* wild type tumors [11–14], while patients with *RAS* mutated tumors often will receive the VEGF targeting antibody bevacizumab [15, 16]. The objective response rate to first-line systemic treatment of mCRC patients approximates 50 % [10, 17]. However, only 10 % of mCRC patients will obtain objective response during second-line treatment [10], suggesting that there is a high degree of cross-resistance between the used drugs. Improvements in mCRC treatment may be achieved through the development of novel drugs with new molecular mechanisms of action and thus lack of cross-resistance with currently used drugs. However, drug development is expensive (estimated cost is 1 Bill USD per drug), takes a long time (12–15 years) and the risk of failure in late stage clinical trials is extremely high. An alternative to the drug development approach is to search for novel predictive biomarkers that can guide personalized treatment and thereby select the right drug for the right patient at the right time. Using predictive biomarkers will increase the therapeutic index and avoid side effects among the many patients who will not benefit from the treatment. A third way to address these medical problems is to test whether drugs being used in some other cancer types might have beneficial effects also in CRC. However, with an expected relatively low response rate, such drugs should only be used together with companion diagnostics allowing for a pre-treatment selection of patients with the highest likelihood of obtaining benefit from the treatment. This third approach is called biomarker guided repurposing and is the foundation for the present protocol, where we investigate whether epirubicin has a beneficial effect in oxaliplatin resistant mCRC patients with *TOP2A* gene amplification.

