This study differs from the standard treatment strategy for mCRC, where the patients often will be offered irinotecan-based therapy after failure to oxaliplatin-based therapy or vice versa. Median PFS of this standard treatment is approximately 2 months, and 75 % of the patients will experience progressive disease after 4 months of treatment [10]. In the present phase II protocol with pre-selected patients, we expect that 30 % will have objective response after the first 4 months of treatment, thereby achieving an increased median PFS. All patients will be evaluated every 9 weeks, enabling a quick change in treatment strategy if a patient experiences disease progression during epirubicin treatment [32, 33]. Carefully planned and closely monitored “window of opportunity” phase II studies are feasible and ethically acceptable in mCRC patients, and may have the advantage to determine potential efficacy of novel agents without placing the patients at risk. In the present study, close monitoring of efficacy every 9 weeks will ensure that this novel treatment line with epirubicin will be offered without further delay in case of progression during epirubicin treatment, with respect to any future treatment option.

The statistical basis for the protocol is based on the fact that we expect a response rate of 30 % in this sub-population of patients with *TOP2A* aberrations, which is significantly better than the typical second line treatment these patients will be offered, which usually has response rates of 10 %. In conclusion, if the objectives of this study protocol are met, the expected 10 % of mCRC patients with a TOP2A/CEN-17 ratio ≥ 1.5 will be offered an extra line of effective treatment, which may lead to an overall improved survival in this subgroup of mCRC patients.

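### The 10% and 30% rates are justified as response rates but applied to tumor control, so a go decision shows control above a 10% floor and not parity with second-line therapy

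*Protocol article*

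**What the plan says.** **Decision rule (Protocol article, Statistics).** The design is a Simon minimax two-stage design with 15 + 10 patients, α = 0.05 and 80% power. The lower rate is set by "A tumor control rate less than 10 % after 4 months", which is judged "after 4 months (at the time of the second evaluation CT scan) is not clinically relevant". The upper rate appears in the final rule: with 5 of 25 patients controlled, "a tumor control rate of 30 % cannot be rejected", and the treatment is taken as good enough for further study. Tumor control means partial response or stable disease at the second scan, after six courses.

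**Where the rates come from (Background and Discussion).** The Background says that only 10% "of mCRC patients will obtain objective response during second-line treatment". The last part of the Discussion names the statistical basis of the protocol as an expected response rate of 30%, against 10% for typical second-line treatment, and calls the former significantly better. Earlier, the Discussion describes the 30% as objective response after the first 4 months.

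**Benchmarks for time to progression.** The Discussion says of standard treatment: "Median PFS of this standard treatment is approximately 2 months", and that 75% "of the patients will experience progressive disease after 4 months of treatment". The Statistics section says: "In randomized trials on second-line therapy, PFS is around 4 months".

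**The concern.** Objective response and tumor control are different events, and tumor control is the more frequent one because it adds stable disease. A null rate taken from objective response is therefore too low to stand for standard therapy when the count includes stable disease. No section supports 10% as the control rate of standard second-line treatment, and the Discussion's own progression figures point to a rate about two and a half times as high.

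What is at stake is the meaning of a positive trial. If the rule readily passes a drug that merely equals standard therapy, success cannot support the Discussion's comparison with second-line treatment. Early stopping would also give little protection against such a drug.

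**Working it through.** **Inputs.** From Statistics: p0 = 0.10, p1 = 0.30, α = 0.05 (taken as one-sided, the usual form of a Simon design), power 0.80, stages 15 + 10. Printed rule: continue if at least 1/15, success if at least 5/25. From the Discussion: 75% progressed after 4 months; median PFS about 2 months.

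**Formula.** With X1 ~ Bin(15, p) and X2 ~ Bin(10, p), and continuation when X1 > r1:

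P(go) = Σ over x > r1 of P(X1 = x) × P(X2 ≥ k − x), where k is the total needed for success.

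**1. Reproduce the design.** An exhaustive minimax search for 10% against 30% gives n1 = 15, n = 25, stop at ≤1/15, success at ≥6/25, with type I error 0.033 and power 0.802. The sample size and stage sizes match the plan. Both printed cut-offs lie one below these boundaries; with them the type I error is 0.098 and power 0.909. That is a separate error, so both rules are carried below.

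**2. Control rate on standard therapy implied by the plan.**
- Complement of the stated progression: 1 − 0.75 = 0.25.
- 2-month median with exponential PFS, at 4 months: 0.5^(4/2) = 0.25. The two Discussion figures agree.
- Same median at the second scan, six courses × 3 weeks = 18 weeks = 126/30.44 = 4.14 months: 0.5^(4.14/2) = 0.238.
- If the Statistics figure of 4 months is a median (the text does not say so), at 4 months: 0.5^(4/4) = 0.50.

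**3. Probability of a go decision at those rates.**

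| True control rate | Minimax boundaries (≥2/15, ≥6/25) | Printed cut-offs (≥1/15, ≥5/25) |
|---|---|---|
| 10% | 0.033 | 0.098 |
| 23.8% | 0.562 | 0.743 |
| 25% | 0.616 | 0.785 |
| 30% | 0.802 | 0.909 |
| 50% (only if 4 months is a median) | 0.998 | >0.999 |

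**4. Early stopping at 25%.** Under the printed rule: 0.75^15 = 0.013. Under the minimax rule, P(X1 ≤ 1) = 0.080. Neither is likely to stop a drug at the benchmark rate.

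**5. Could the null simply be raised to 25%?** With 25 patients, stopping at ≤3/15 and requiring ≥11/25 gives type I error 0.030. Power is 0.098 at the plan's 30% target, 0.787 at 50% and 0.815 at 51%. Keeping a 20-point difference (25% against 45%, where 45% is an assumption) needs 36 patients in a minimax design.

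**The case against.** The strongest reply is that the Statistics section never calls 10% a response rate. It defines 10% as the level of tumor control below which activity has no clinical interest, and a go decision leads only to further studies. A proof-of-concept screen may set its floor below active standard care, and the Discussion may simply be using the word response loosely. The Discussion also presents epirubicin as an extra line of treatment, for which activity without cross-resistance could be worthwhile even if it did not beat irinotecan.

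Much of this stands. A floor of 10% is a permissible choice, and passing a drug as active as standard therapy is not in itself a fault in such a screen. What does not survive is the combination of that floor with the Discussion, which bases the statistics on response rates and on being better than second-line treatment.

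Three further limits stand. The 25% describes standard treatment after oxaliplatin failure; the inclusion criteria as printed set no limit on prior lines, so the enrolled patients could have a lower control rate. The 50% scenario depends on reading an unlabelled PFS figure as a median. And 0.785 should not be blamed on the null alone, since it includes the boundary error.

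A reader might infer that the trial would usually declare an ineffective drug effective, or that 25% is the only valid null. The documents support neither: the formal conclusion is limited to continuing research, and a drug with 25% control is not inactive.

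**Conclusion.** The point holds in a limited form. The rates and the counted event do not match: the Discussion justifies 10% and 30% as response rates, while the rule applies them to response plus stable disease. At the control rate implied by the plan's own figures for standard therapy (23.8–25%), a go decision has probability 0.56–0.62 with the boundaries that fit the design. Correcting the cut-offs alone therefore does not remove the problem. A go result supports control above 10% and nothing stronger.

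This rests on three assumptions: that 75% progressed after 4 months means by 4 months, which the 2-month median supports; that patients without progression count as controlled; and, for the 18-week figure only, that PFS is exponential. The 2-month and 4-month benchmarks conflict on any reading that takes both as typical PFS for second-line therapy, and the longer one would widen the gap.

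**What to change.** First reconcile the 2-month and 4-month PFS benchmarks, saying what each figure is (median or otherwise) and which population it describes. Then make rates and event agree within N = 25, in one of two ways.

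- **Count objective response (CR + PR) against 10%/30%**, with stop at ≤1/15 and success at ≥6/25 (type I error 0.033, power 0.802). Cost: the decision moves to an event that the plan lists as secondary and that is further from the primary endpoint of PFS.
- **Keep tumor control and describe 10% as a minimum-activity floor** lying below the roughly 25% benchmark. Correct the Discussion so that it neither calls these rates response rates nor claims an advantage over second-line therapy, and state the 56–62% go probability at the benchmark. That range assumes the boundaries are corrected; with the printed cut-offs it is 74–79%. Cost: text changes, and acceptance that a go result makes no comparison with standard care.

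Either way the hypothesis text and boundaries need an amendment. The Trial status section reports 3 patients treated, so this can be done before the first-stage decision. Moving the null to 25% with success at ≥11/25 is not a cheap alternative: power is 9.8% at the stated 30% target and reaches about 80% only near 50% control.

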**Methods/Design:**

The study is an open label, single arm, phase II study, investigating the efficacy of epirubicin in patients with oxaliplatin refractory mCRC and with a cancer cell *TOP2A*/CEN-17 ratio ≥ 1.5. *TOP2A* gene amplification measured by fluorescence in situ hybridization. A total of 25 evaluable patients (15 + 10 in two steps) will be included (Simon’s two-stage minimax design). Every nine weeks, response is measured by computed tomography imaging and evaluated according to RECIST 1.1. The primary end-point of the study is progression-free survival.

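### The stage 1 cohort is defined in two incompatible ways, and the evaluable-patient reading drops some treated failures from the denominator

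*Protocol article*

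**What the plan says.** The Statistics section sizes the trial in evaluable patients: "The number of evaluable patients (the sample size) is based on Simon’s two stages Mini-max design". The Abstract (Methods/Design) gives the total the same way: "A total of 25 evaluable patients (15 + 10 in two steps) will be included". Neither place defines evaluable.

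Two consecutive ideas in the Statistics section then identify the stage 1 patients:

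- Accrual rule: "The enrolment will continue until 15 patients have completed the second CT scan or experienced progressive disease".
- Stopping rule: "If none out of the first 15 consecutive patients achieve stable disease at the second CT scan", in which case the study closes.

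For stage 2 the text says only that 10 more patients are accrued, and the final rule refers to 5 of 25. The criterion of a second CT or progression is written for stage 1 alone.

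Two other sections bear on who meets that criterion. Treatment lists toxicity and the patient's wish, besides progression and the cumulative dose limit, as reasons for ending epirubicin. Study objectives defines the PFS event as documented RECIST progression and does not mention death.

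**The concern.** A treated patient who has neither a second CT nor documented progression does not count toward the 15 under the accrual rule, so enrolment runs on until someone else does. No replacement rule is written, but that is the effect. Such a patient has not shown tumor control at the second scan and, for a go/no-go decision, is a failure. Leaving failures out can only raise the observed rate.

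Under the stopping rule, the same patient could be one of the first 15 and would count. The two cohorts diverge as soon as one patient is lost, or as soon as a later enrollee progresses at week 9 before an earlier one reaches the second scan. The stage 1 decision turns on zero versus at least one patient with control, so the membership of a single patient can decide whether the trial stops.

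Some losses of this kind are plausible: eligibility admits performance status 2 and a life expectancy of 3 months, while the endpoint is read at about 4 months. The document gives no figure for them.

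**Working it through.** **Inputs from the Statistics section.** Null rate p0 = 0.10 ("A tumor control rate less than 10 % after 4 months" is called not clinically relevant); target p1 = 0.30 ("a tumor control rate of 30 % cannot be rejected"); "Assuming a significance level at 0.05 (α = 0.05) and a power at 80 % (β = 0.20"; n1 = 15, n = 25. Sidedness is not stated; one-sided is used, as is usual for a Simon design.

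**Step 1: reproduce the sample size.** With X1 ~ Bin(15, p) and X2 ~ Bin(10, p), and with the trial continuing if X1 ≥ a and succeeding if X1 + X2 ≥ c,

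P(success) = Σ over x ≥ a of P(X1 = x) · P(X2 ≥ c − x).

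A search for the smallest n with alpha ≤ 0.05 and power ≥ 0.80 returns n1 = 15, n = 25, a = 2, c = 6, with alpha 0.0328 and power 0.8017. The 15 + 10 split is therefore reproduced. The cut-offs as written (a = 1, c = 5) are each one lower and give alpha 0.0977 and power 0.9088 with no losses at all.

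**Step 2: effect of counting evaluable patients only.** Let d be the fraction of treated patients with neither a second CT nor progression. The value of d is an assumption. Assume also that none of these patients has tumor control and that all are replaced. The control rate among evaluable patients is then 0.10/(1 − d); for example, 0.10/0.80 = 0.125 at d = 20 %. Putting that rate into the formula gives:

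| Assumed loss d | Evaluable rate | Alpha, standard limits (≥2/15, ≥6/25) | Alpha, cut-offs as written (≥1/15, ≥5/25) | Treated to reach 25 evaluable, 25/(1 − d) |
|---|---|---|---|---|
| 0 % | 10.0 % | 0.033 | 0.098 | 25 |
| 5 % | 10.5 % | 0.041 | 0.115 | 26.3 |
| 10 % | 11.1 % | 0.051 | 0.137 | 27.8 |
| 20 % | 12.5 % | 0.082 | 0.195 | 31.2 |
| 30 % | 14.3 % | 0.134 | 0.280 | 35.7 |

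The standard-limits column isolates the effect of evaluability. The last alpha column starts from 0.098, which comes from the cut-offs and not from the denominator. At 20 % loss, 5 of 25 evaluable patients corresponds to 5/31.2 = 16 % of those treated.

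**Step 3: power if all treated patients are counted.** If the 30 % target was meant for evaluable patients, the all-treated target at 20 % loss is 0.30 × 0.80 = 0.24. Power then falls from 0.80 to 0.57 under the standard limits, and from 0.91 to 0.75 under the cut-offs as written.

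**Step 4: over-run.** No pause at 15 enrolled is stated, so patients can enter while outcomes are awaited. In a simulation at an assumed accrual of one patient a month, about 18 are enrolled when the 15th outcome arrives; at one every two months, about 16.5. The text then adds 10 more, so it is unclear whether the extra patients count and whether the final denominator is 25.

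**The case against.** The strongest reply is that replacement is inferred. No replacement rule is written, and the stopping rule can be read as already using the non-selective cohort, with the accrual sentence only timing the interim look. The criterion is spelled out for stage 1 only. The article is also condensed, and analysis sets are commonly left to the full protocol or SAP. The first two points stand, and they are why the finding is an inconsistency and not a proven exclusion. The last does not dispose of it: the article states the go/no-go rule and gives it two denominators, which is more than missing detail.

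The affected group is also narrow. A patient who stops epirubicin early but still has the second CT, or who progresses, is counted and causes no bias. Nothing in the document says that scanning ends with treatment. This stands.

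Three stronger readings are tempting and are not supported:

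- A reader might infer that the design's alpha is broken. That depends on an unstated loss rate; under the standard limits alpha is still 0.041 at 5 % loss and 0.051 at 10 %.
- A reader might attribute the whole 0.098 to 0.280 series to evaluability. The 0.098 arises with no losses, from the written cut-offs, which are a separate defect.
- A reader might infer that running past 15 inflates the false-positive rate. It does not. Progressors can qualify at week 9 and controlled patients only at the second scan, so taking the first 15 to qualify would, if anything, lower the stage 1 rate (about 9.2 to 9.4 % against a true 10 % in a simulation at one patient a month). A Simon design does not require accrual to pause.

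**Conclusion.** The concern holds in limited form. The Statistics section gives the stage 1 decision two incompatible cohorts, and the evaluable one biases the tumor control rate upward by leaving out treated patients with neither a second CT nor progression. Under the standard minimax limits, alpha moves from 0.033 to about 0.05 at 10 % loss, 0.082 at 20 % and 0.134 at 30 %. These figures assume a true all-treated rate of 10 %, that every lost patient lacks control, that lost patients are replaced in both stages, and loss rates that the document does not supply. For stage 2, replacement rests only on the Abstract's phrase "A total of 25 evaluable patients". Over-run affects the early stop and the clarity of the final denominator, not the false-positive rate.

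**What to change.** 1. Define the two cohorts as the first 15 and the first 25 consecutive patients who received at least one dose of epirubicin, and use that definition in the accrual rule, the stopping rule, the final rule and the Abstract.
2. Score anyone without tumor control documented at the second evaluation, including death or a missing CT, as no tumor control. Report the evaluable-only rate as a sensitivity analysis.
3. State that patients enrolled while the 15th outcome is awaited count toward the 10 of stage 2, so that the final denominator is 25.
4. State that the 10 % and 30 % rates refer to all treated patients, or restate the power.

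The cost is mostly wording, and Trial status reports only 3 patients included so far. The reported rate will be slightly less favourable. If the 30 % target was meant for evaluable patients, there is also a real loss of power (0.80 to 0.57 at 20 % loss under the standard limits), which is why item 4 is needed. The change does not bring the written cut-offs to alpha 0.05: with every treated patient counted they still give 0.098, and that has to be dealt with separately.

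### The stage 1 stop rule counts stable disease only, the continue rule counts partial response or stable disease, so a stage 1 with partial responses and no stable disease meets both

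*Protocol article*

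**What the plan says.** All the decision rules are in the Statistics section of the protocol article.

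- **Design.** The sample size "is based on Simon’s two stages Mini-max design", with 15 patients in stage 1 and 10 more in stage 2. The quantity tested is a tumor control rate at the second CT scan, with 10 % as the uninteresting level and 30 % as the target.
- **Stop after stage 1.** "If none out of the first 15 consecutive patients achieve stable disease at the second CT scan", the hypothesis is rejected and the study closes.
- **Continue to stage 2.** "If one or more patients achieve tumor control (partial response or stable disease) at the second scan", 10 further patients are accrued.
- **Final rule.** With 5 of 25 patients in tumor control after six courses, "a tumor control rate of 30 % cannot be rejected" and the treatment is judged worth further study.

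The bracket in the continue sentence is the only place where tumor control is spelled out. Complete response is not named anywhere in the article. The Discussion describes the same 30 % as patients who "will have objective response after the first 4 months of treatment".

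**The concern.** The stop and continue sentences should be complements: exactly one of them should apply to any stage 1 result. They are not, because they count different things. The article evaluates response by RECIST 1.1, where partial response and stable disease are separate categories, so a partial responder is not literally a patient with stable disease. A stage 1 with responders but no stable disease therefore meets both conditions.

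This matters because the two-stage rule is the trial's only formal decision; PFS and OS are to be reported as Kaplan-Meier medians without a test. Followed literally, the stop sentence could close the study because patients did better than stable disease. The trial is also open label with a single arm, so a choice between two conflicting written rules would be made with the results in view.

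**Working it through.** **Inputs from the Statistics section:** alpha 0.05 (sidedness not stated, taken as one-sided), power 80 %, uninteresting rate 10 %, target rate 30 %, stage 1 size 15, total 25. **Not in the article:** the split of tumor control into partial response (PR) and stable disease (SD). It is an assumption below and is shown as a range. Complete response is set to zero, and patients are treated as independent.

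**1. The plan's own figure.** An exact binomial search for the minimax design with these inputs gives 15 patients in stage 1 and 25 in total (stop at 1 or fewer of 15, success at 6 or more of 25), with alpha 0.0328 and power 0.8017. The stage sizes reproduce.

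**2. The two stage 1 sentences side by side.**

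| Stage 1 result (15 patients) | Stop sentence met? | Continue sentence met? |
|---|---|---|
| No SD, no PR, no complete response | yes | no |
| At least one SD | no | yes |
| No SD, at least one PR | **yes** | **yes** |
| No SD, no PR, at least one complete response | yes | no |

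Only the third row is a contradiction. The fourth row is a different matter: the literal text gives one answer, stop, because complete response lies outside the written gloss.

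**3. Probability of the contradiction.** With PR probability *pr* and SD probability *sd*,

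P(no SD and at least one PR) = (1 − sd)^15 − (1 − sd − pr)^15.

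At a true tumor control rate of 30 % the second term is always 0.70^15 = 0.0047.

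| Assumed PR / SD | P(no SD) = (1 − sd)^15 | P(both sentences met) |
|---|---|---|
| 5 % / 25 % | 0.75^15 = 0.013 | 0.009 |
| 10 % / 20 % | 0.80^15 = 0.035 | 0.030 |
| 15 % / 15 % | 0.85^15 = 0.087 | 0.083 |
| 20 % / 10 % | 0.90^15 = 0.206 | 0.201 |
| 25 % / 5 % | 0.95^15 = 0.463 | 0.459 |
| 30 % / 0 % | 1 | 0.995 |

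The middle column is also the probability that the study closes if the stop sentence is given priority. If the continue sentence has priority, it closes with probability 0.0047 in every row.

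At a true rate of 10 %, the contradiction has probability 0.037, 0.105, 0.257, 0.478 and 0.794 when responders make up 10, 25, 50, 75 and 100 % of controlled patients.

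**4. After one shared definition.** With the written cut-off of none in 15 kept, the two sentences are complements and the probability of contradiction is zero. The study then stops at stage 1 with probability 0.90^15 = 0.206 at a true rate of 10 % and 0.0047 at 30 %.

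**The case against.** The strongest reply is that the intended meaning can be recovered. The design tests a tumor control rate, early termination is for insufficient effect, and both the continue sentence and the final rule count tumor control. The stop sentence then reads naturally as no patient reaching at least stable disease. A sensible team would continue after a partial response. This is probably what the authors meant, and it keeps the point modest. It does not remove it: the article states both rules in full, they disagree, and a pre-specified stopping rule should not rest on inferred intent.

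A second reply is that the large probabilities need control to be mostly response. The Background puts second-line objective response at about 10 %, and the Discussion says epirubicin had less impact than standard options in unselected patients. At 10 % PR and 20 % SD the conflict is only 3 %. This stands. The 99.5 % figure depends on taking the Discussion's objective-response wording at face value, and the same section benchmarks against the share of patients progressing by 4 months, so that wording may be loose.

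Two stronger readings are tempting, and the article does not support them.

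- **That omitting complete response also causes the stop-and-continue clash.** It does not: a stage 1 with complete responses only meets the stop sentence alone. The gloss is also a brief bracket, and few investigators would deny that a complete response is tumor control.
- **That omitting complete response costs the trial its power.** If 2 of the 30 percentage points were complete responses scored as failures, power under the reproduced minimax boundaries would fall from 0.802 to 0.736. But those boundaries are not the written ones. With the written cut-offs (stop at 0 of 15, success at 5 of 25) it goes from 0.909 to 0.869, still above 80 %. The 2-point share has no source in the article either.

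**Conclusion.** The point holds as an inconsistency in a stated decision rule. A stage 1 with at least one partial response and no stable disease is told both to close and to accrue 10 more patients. At a true tumor control rate of 30 % the chance of this runs from about 1 % to 46 % over assumed splits from 5/25 to 25/5, and reaches 99.5 % only if all control is response. The documents do not say where in that range the trial lies, so no single figure should be quoted as the risk.

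The omission of complete response is a separate and lesser point: read literally, a complete responder would not count in the stage 1 rules or in the 5-of-25 rule. No loss of power should be claimed from it.

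The mismatch between the written cut-offs and the reproduced minimax boundaries, and that between tumor control in Statistics and objective response in the Discussion, are separate issues and this conclusion does not rest on them.

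**What to change.** Define tumor control once, as complete response, partial response or stable disease by RECIST 1.1 at the second CT scan. Use that term, and no other, in three places:

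- the stage 1 stop rule: no patient among the first 15 with tumor control;
- the stage 1 continue rule: one or more of the first 15 with tumor control;
- the final rule on 25 patients.

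The cost is one definition and a rewording of the stop and continue sentences. The sample size stays at 15 + 10 = 25, and no visit or scan changes. The Trial status section reports 3 patients on treatment, so at the time of the article the change could be made well before the 15-patient look.
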